## Abstract

Approximately 2%-12% of individuals aged > 65 years worldwide are estimated to have an abdominal aortic aneurysm (AAA), with a mortality rate exceeding 60% in rupture cases. The sole preventive intervention against rupture is timely surgery, which requires substantial medical resources, including postoperative complication management. Although numerous randomized clinical trials have been performed, no oral medication effectively treats AAA. Tricaprin, a medium-chain triglyceride with 3 capric acids, is used in dietary therapy for metabolic and neurological disorders. Our group recently reported that tricaprin, unlike other medium-chain triglycerides, showed reverse remodelliing of AAA in a rat model. Determining whether this basic finding could be translated to clinical practice is important. The **F**irst-in-**H**uman **A**bdominal **A**ortic **A**neurysms trial with **T**ricaprin (F-HAAAT) proposes the first-in-human AAA trial to confirm the safety of tricaprin use in patients with small AAA, exploring novel assessment methods to evaluate treatment efficacy. This single-centre, open-label, single-arm study will include 10 patients (aged 50–85 years) with small AAA (30–45 mm in diameter) receiving daily oral tricaprin (1.5–3.0 g/d) for 52 weeks. Primary endpoints include safety evaluation of tricaprin determined by monitoring all adverse events, particularly major adverse cardiovascular events, AAA-related adverse events, and other unpredictable events. Secondary endpoints include parameters to validate tricaprin efficacy by measuring AAA diameter, volume, and Agatston score, and analyzing computed tomography values of the aortic aneurysmal wall. Outcomes of the trial may provide insights into noninvasive methods for indirectly analyzing AAA pathologic characteristics and revealing aneurysmal reverse remodelliing (jRCTs051240036, Japan Registry of Clinical Trials).

Abdominal aortic aneurysm (AAA) is a prevalent cardiovascular condition affecting approximately 2%-12% of individuals aged > 65 years worldwide.^1^ Left untreated, AAA can progressively expand asymptomatically, culminating in a potentially fatal rupture in 0.04 persons/100 person-years^2^ or < 5%^3^ per year in those with small AAA.^4^ Current treatment options primarily involve surgical interventions, such as open surgical repair or endovascular aneurysm repair, which carry inherent risks and are associated with long-term complications.^5^ Recent data indicate a 30-day mortality rate of 24.7% after emergency surgery for ruptured AAA, with a major adverse cardiovascular events (MACE) rate of 20.2%. In contrast, the 30-day mortality rate for elective surgery in unruptured AAA ranges from 1.0% in patients aged < 70 years to 10%, even in those aged > 70 years, underscoring the importance of preventing AAA rupture through use of medication.^6^, ^7^, ^8^ Thus, a considerable unmet medical need is for effective and noninvasive therapies for AAA management.

Developing noninvasive AAA treatments requires identifying the mechanisms and active compounds that bridge the translational gap between animal studies and clinical practice. Despite advancements in the understanding and imaging of AAA pathophysiology, previous randomized controlled trials^9^, ^10^, ^11^, ^12^, ^13^, ^14^, ^15^, ^16^ in humans have failed to translate the therapeutic effects observed in conventional animal models—such as those using angiotensin II injection, porcine pancreatic elastase administration, and calcium salts application^17^—into clinical success. In the course of resolving this translational gap, through the findings obtained from the analyses of human AAA specimens, we found that inducing hypoperfusion in the abdominal aortic wall can induce AAA in rats.^18^ This model closely resembles human AAA, with vasa vasorum stenosis, increased vasa vasorum, ectopic adipocytes, intraluminal thrombi, and a high rupture rate. Aortic hypoperfusion with ischemic reaction, also described in human AAA, is now recognized as a critical pathogenic mechanism^19^ that could contribute significantly to AAA formation. We previously validated the influence of several agents^20^, ^21^, ^22^, ^23^, ^24^, ^25^ on aortic degeneration in the context of seeking medical treatment for AAA. Among these candidates, our 2023 report on the effect of tricaprin on preventing AAA development presented notable results. In an animal aortic hypoperfusion model, oral administration of tricaprin before the AAA induction procedure almost completely abrogated the induction of AAA without resolving the hypoperfusion of the aortic wall.^26^ Tricaprin, composed of 3 capric acids (C-10 medium-chain fatty acids) and 1 glycerol, is a nutritional ingredient in breast milk^27^ and coconut oil.^28^ We reported that tricaprin had a promising effect on myocardial lipolysis^29^ and diffuse coronary stenosis^30^ in patients with triglyceride deposit cardiomyovasculopathy. Tricaprin reduces excessive triglyceride accumulation in vascular smooth muscle cells. Given that triglyceride accumulation in the adventitia of AAA has been confirmed and is associated with rupture rate,^31^ tricaprin use may be effective in treating vascular diseases, including AAA.

Building on the pathologic features of human AAA, findings from the aortic hypoperfusion rodent model, and results from the tricaprin experiment, we designed the First-in-Human Abdominal Aortic Aneurysms trial with Tricaprin (F-HAAAT). This study aims to evaluate the safety of tricaprin use in patients with AAA and explore potential indicators of its efficacy. By analyzing changes in the Agatston score and aortic aneurysm wall, computed tomography values (AAWCVs) before and after tricaprin administration, we aim to characterize the histologic changes within the AAA wall comprehensively. This goal includes evaluating classical parameters, such as aneurysm diameter and volume, focusing on the presence of aortic perfusion defects. The AAWCV method was developed to noninvasively analyze the pathology of AAA by classifying the computed tomography (CT) values of AAA components into 6 groups and monitoring the volume changes in each category to indirectly assess histologic changes. Although the reverse remodelliing effect of tricaprin on AAA remains uncertain, owing to the small number of participants and short evaluation duration in this trial, we expect that AAWCV will be a suitable indicator for evaluating histologic alterations. The F-HAAAT study was designed to establish a new paradigm for AAA treatment, based on scientific evaluation and innovative imaging techniques.

## Materials and Methods

### Materials

CAPRINHI, a dietary supplement containing 99.2% tricaprin, with one tablet (400 mg) being equivalent to 250 mg of tricaprin, was provided by Tochino Foundation (Osaka, Japan).

### Study design

This is a single-centre, open-label, and single-arm trial designed to investigate the safety of oral tricaprin 3 g/d for patients with AAA and explore potential indicators of efficacy. Patients with AAA who meet all the inclusion criteria and no exclusion criteria will be eligible for enrollment. A schematic representation of the trial is shown in Figure 1. Candidates will be recruited from an outpatient population diagnosed with asymptomatic infrarenal AAA. Tricaprin safety will be evaluated for all adverse events throughout the trial period. Additionally, efficacy indicators will be explored using abdominal CT findings. No post-treatment follow-up evaluation is planned.

**Figure 1 fig1:**
[figure not shown]
Trial scheme. The "pre-trial observation period" for screening before tricaprin administration shall not exceed 8 weeks. After tricaprin initiation, a 2-week follow-up period (initiation period) will follow, to rule out unexpected side effects. After initiation, patients will be monitored every 3 months and treated with tricaprin for 52 weeks. Contrast-enhanced computed tomography (CT) will be performed at the screening visit and visit 5, whereas unenhanced CT will be performed at the screening visit, visit 3, and visit 5.

### Study population

This study will include individuals aged 50-85 years who have a diagnosed small AAA under conservative follow-up treatment and will provide written informed consent. Eligible participants must have evidence of having a AAA with a maximum minor short-axis diameter (MMSD) of ≤ 45 mm on a contrast-enhanced CT scan performed within 5 weeks before or 8 weeks after they provide consent. All eligibility assessments will follow participant provision of informed consent. A total of 10 individuals will be included. Exclusion criteria include having any of the following: a prior aortic repair (endovascular or open); surgery for AAA scheduled for within a year; dissecting or severely calcified AAA; or an estimated glomerular filtration rate of < 30 mL/min. A complete list of eligibility criteria is provided in Table 1.

**Table 1 tbl1:** Eligibility criteria

Inclusion criteria
• Aged 50–85 years at the time of consent
• Patients diagnosed with infrarenal AAA with a diameter of 30–45 mm according to enhanced CT scanning∗
• Provision of written informed consent directly from the patients
**Exclusion criteria**
• History of AAA surgical repair, including endovascular treatment
• Patients scheduled for surgical treatment for AAA within a year
• Symptomatic AAA
• AAA location excluding the infrarenal abdominal aorta
• Sac-type AAA
• Infected AAA or evident active aortitis
• Dissecting AAA
• Severely calcified AAA
• Heart failure symptoms of New York Heart Association classification III–IV
• Prognosis of < 2 y
• Estimated glomerular filtration rate ≤ 30 mL/min
• Bronchial asthma on treatment† or diagnosed with NSAIDs-exacerbated respiratory disorder
• History of contrast agent allergy
• AAA associated with connective tissue diseases (Ehlers–Danlos syndrome, Marfan syndrome, Loeys–Dietz syndrome)
• Consumed foods, including food oils labeled as “MCT” in their commercial names and containing medium-chain fatty acids, at least once daily for > 2 mo, and are unable to discontinue their use by the day before tricaprin initiation
• Diagnosed with familial hypercholesterolemia
• Unable to express their own will and manage the investigational substances on their own (eg, dementia)
• Others deemed ineligible for participation by the principal investigator or co-investigator

AAA, abdominal aortic aneurysm; CT, computed tomography; MCT, medium-chain triglyceride; NSAID, nonsteroidal anti-inflammatory drug.

∗ The CT Images performed up to 5 wk before or up to 8 wk after consent can be used for screening.

† Except for the cases without an asthma attack for > 5 y.

### Treatment protocol and study assessments

All participants will receive 1.5 g/d tricaprin for the first 2 weeks until visit 1, after which the dose will be increased to 3.0 g/d and maintained until week 52, administered in 3 divided doses per day. Participants unable to tolerate this increase will be excluded from further analyses. Lifestyle management, smoking cessation, and adjustment of metabolic and cardiovascular medications will be encouraged. Participants will visit the investigator quarterly to assess their symptoms, their experience of MACE, aneurysmal exacerbations, and side effects based on vital signs, adverse events, medication compliance, concomitant medication use, safety tests, and abdominal CT scans. Visits from visit 2 onward will be scheduled approximately every 3 months, with a 14-day flexibility period allowed. Contrast-enhanced and unenhanced CT scans at screening and visit 5 will measure the aneurysmal diameter, volume, Agatston score, and AAWCV. Visit 3 will include an unenhanced CT scan to check for abrupt expansion (≥ 5 mm over 6 months). Electrocardiograms will be conducted at the beginning and end of the trial to screen for asymptomatic cardiovascular complications. Tricaprin consumption will be monitored at each visit by using a patient diary and measuring the change in the weight of the tricaprin bottle. A tricaprin consumption rate of > 60% will be set as the threshold for the secondary endpoint sensitivity analysis. Figure 2 outlines the trial process (patient flowchart). Table 2 presents the data collection schedule.

**Figure 2 fig2:**
[figure not shown]
Patient flowchart. The patient flowchart outlines the trial process. All participants who provide informed consent will undergo screening tests. Patients will be excluded if they are found to be ineligible based on screening, unable to tolerate the increase in tricaprin from 1.5 to 3.0 g/d, show concerning computed tomography (CT) findings at visit 3, experience severe adverse events, request withdrawal, or are deemed ineligible at any visit for other reasons. AAA, abdominal aortic aneurysm; MMSD, maximum-minor short-axis diameter After initiating tricaprin use at 3, ∗ After initiating tricaprin use at 3.0 g/d, the trial may be discontinued if any abnormal findings warrant cessation, even between scheduled visits.

**Table 2 tbl2:** Data collection schedule

Study item, data collection, or activity	Informed consent	Screening visit	Day 0	Day 1	Visit 1	Visit 2	Visit 3	Visit 4	Visit 5	Cessation
Day of performance, d	—	–56 to –1	0	1	14	91	182	273	364	—
Allowance period, d	—	—	—	—	± 7	± 14	± 14	± 14	± 14	+ 28
Informed consent	X	X	—	—	—	—	—	—	—	—
Patient’s background	—	X	—	—	—	—	—	—	—	—
Eligibility confirmation	—	X	—	—	—	—	—	—	—	—
Tricaprin administration, g	—	—	—	1.5	➡	3.0	➡	➡	➡	—
Adherence check	—	—	—	—	X	X	X	X	X	X
Comorbidities/Medical history	—	X	—	—	—	—	—	—	—	—
Abdominal contrast CT scan	—	X	—	—	—	—	—	—	—	X
Abdominal unenhanced CT scan	—	X	—	—	—	—	X	—	—	X
Clinical findings		X	X	—	X	X	X	X	X	X
Laboratory test		X	X	—	X	X	X	X	X	X
Electrocardiogram		X	—	—	—	—	—	—	X	X
Adverse events		—	—							

The shorter arrows indicate the same dosages as those shown on the left side of each one. The longer arrow represents the continuous monitoring of adverse events between visits.

CT, computed tomography.

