### Study endpoints and statistical assessments

The primary endpoint is the safety of oral tricaprin for 52 weeks, as determined by analysis of the occurrence rate of adverse events, specifically the following: (i) MACE incidence; MACE includes cardiovascular death, nonfatal myocardial infarction, and nonfatal stroke.; (ii) AAA exacerbation; adverse events related to AAA exacerbation include nonfatal acute abdomen with proven AAA rupture, nonfatal acute abdomen without overt AAA rupture, a sudden change in skin color, or edema of the lower limbs with severe pain, and an abrupt need for surgical intervention; and (iii) unpredictable tricaprin side effects; unpredictable tricaprin side effects include miscellaneous events presumably related to tricaprin use and not attributable to (i) or (ii). These events will be assessed via physical examinations, vital sign assessments, safety laboratory tests, physiological tests, and abdominal CT scans. In particular, for MACE, AAA exacerbation, and unpredictable side effects following administration of tricaprin, the number of occurrences and events and their percentages will be calculated and presented, apart from the total analysis of all adverse events, owing to their clinical importance. Additionally, vital sign measures and laboratory test results will be summarized with descriptive statistics at each visit as a subanalysis. Vital signs include the following: systolic blood pressure (mm Hg); mean blood pressure (mm Hg, calculated using the formula [diastolic pressure + (systolic – diastolic) / 3”]; and heart rate (beats per minute). Laboratory test results will include measures of levels of alanine aminotransferase, gamma-glutamyl transpeptidase, blood urea nitrogen, creatinine, sodium, potassium, chloride, D-dimer, C-reactive protein, and brain natriuretic peptide; a complete blood cell count (white, red, hemoglobin, hematocrit, and platelets); and estimated glomerular filtration rate.

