### Determination of the target for data analysis

The full analysis set will be used for data analysis, including all patients, excluding ineligible cases, with at least one tricaprin administration of 3.0 g/d and visit, regardless of treatment discontinuation during the follow-up period. A sensitivity analysis of secondary endpoints will be scheduled for participants with good compliance to medication use, defined as a tricaprin consumption rate > 60%. This threshold is based on phase 2a trial data,^29^ which showed that patients with triglyceride deposit cardiomyovasculopathy who maintained a tricaprin intake of ≥ 1.5 g/d showed improved clinical outcomes. If participants consume > 60% of tricaprin throughout the trial period, they will have ingested an average daily dose exceeding 1.8 g/d. Therefore, individuals in the sensitivity-analysis group should be considered to have received a dose sufficient to assess tricaprin efficacy.

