### Sample size calculation and statistical considerations

A sample size of 10 participants was selected based on ethical considerations and the exploratory nature of the study. Although medium-chain triglycerides have a well-established safety profile, the safety of tricaprin in patients with AAA remains unverified. Moreover, including many participants in an initial safety assessment trial is unethical. AAAs are clinically diverse, with varying progression rates, and no established efficacy endpoints. Although MMSD is used frequently, sometimes it may not increase over extended periods.^35^ This variability makes the establishment of its clinical significance challenging. Given these factors and the lack of spontaneous reverse remodelliing in AAAs, we have opted not to perform statistical significance tests. Instead, we will summarize our findings using descriptive statistics.

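### Ineligible cases leave the only analysis set with no time limit, and ineligibility can be declared after dosing, so a dosed participant's adverse events can drop out of the primary safety count

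*Protocol article*

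**What the plan says.** Section *Determination of the target for data analysis* defines the set: "The full analysis set will be used for data analysis, including all patients, excluding ineligible cases", and then "with at least one tricaprin administration of 3.0 g/d and visit, regardless of treatment discontinuation during the follow-up period". The removal of ineligible cases carries no criterion and no time point. The article describes no other set for the primary endpoint; the subset with consumption above 60% serves a sensitivity analysis of the secondary endpoints only.

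Under *Study endpoints and statistical assessments*, the article defines what is primary in these words: "The primary endpoint is the safety of oral tricaprin for 52 weeks, as determined by analysis of the occurrence rate of adverse events". *Study design* adds that safety covers all adverse events over the whole trial period.

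The Figure 2 caption (patient flowchart) gives one list of reasons for which patients are excluded. It opens with failure at screening and goes on to those who are "unable to tolerate the increase in tricaprin from 1.5 to 3.0 g/d, show concerning computed tomography (CT) findings at visit 3", and those who "experience severe adverse events, request withdrawal, or are deemed ineligible at any visit for other reasons".

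Three further places bear on the point:
- *Treatment protocol and study assessments* takes participants who cannot tolerate the dose increase out of further analyses.
- Table 1 ends with a criterion that leaves ineligibility to the judgement of the principal investigator or a co-investigator.
- Table 2 schedules confirmation of eligibility at the screening visit only.

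**The concern.** Removing enrolled participants for ineligibility is harmless to a safety analysis only if it rests on facts fixed before the first dose. Here the caption allows ineligibility to be declared at any visit, and the analysis-set section then removes ineligible cases. The judgement can therefore come after an event and with knowledge of it, because the trial is open-label and has one arm.

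Several Table 1 exclusions also describe states that can first arise during treatment, such as a symptomatic or dissecting aneurysm, surgery scheduled within a year, or heart failure symptoms of class III–IV. Some of these overlap with the aneurysm-exacerbation events that the primary endpoint is meant to count. If Table 1 were applied again at a later visit, a safety event could become the ground for removing the person who had it.

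At stake are the numerator and denominator of the primary result in a first-in-human safety trial of 10 patients. There is no control arm, and no significance test is planned, so nothing else in the analysis would reveal the loss.

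**Working it through.** **Step 1. Is there a figure to reproduce?** No. The sample size was chosen, not calculated: "A sample size of 10 participants was selected based on ethical considerations and the exploratory nature of the study". The analysis is descriptive: "we have opted not to perform statistical significance tests". The check is therefore textual, with arithmetic only to show size.

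**Step 2. Follow each post-dose reason in the Figure 2 caption through the other sections.**

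| Reason in the caption | What the other sections say | In the safety count? |
|---|---|---|
| Cannot tolerate 3.0 g/d | *Treatment protocol* takes them out of further analyses | No, by explicit statement |
| Concerning CT at visit 3 | *Criteria for cessation* stops tricaprin on expansion or worrying imaging (with an option to continue until surgery) and mentions no removal from analysis; the analysis set keeps discontinued participants | Yes; caption ambiguous |
| Severe adverse event | Analysis set keeps discontinued participants | Yes; caption ambiguous |
| Withdrawal | Analysis set keeps discontinued participants | Yes; caption ambiguous |
| Deemed ineligible at any visit | Analysis set removes ineligible cases, with no time limit | No, if followed as written |

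The rows marked yes assume that 3.0 g/d and a visit were reached. The first row shows that, for at least one post-dose item, exclusion does mean removal from analysis. The last row is the defect. The clause that keeps people after discontinuation does not protect someone classed as ineligible, because that is a separate removal in the same sentence.

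**Step 3. Size.** Input: n = 10 (*Sample size calculation and statistical considerations*). The documents give no event counts, so the counts below are assumptions. Exact (Clopper-Pearson) 95% limits for x of n are the 0.025 quantile of Beta(x, n−x+1) and the 0.975 quantile of Beta(x+1, n−x). For x = 0 the lower limit is 0 and the upper is 1 − 0.025^(1/n).

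- One affected, all kept: 1/10 = 10%; lower limit 1 − 0.975^(1/10) = 0.25%, upper limit 44.5%.
- That person removed: 0/9 = 0%; upper limit 1 − 0.025^(1/9) = 33.6%.
- Two affected, all kept: 2/10 = 20% (2.5% to 55.6%). Both removed: 0/8 = 0%; upper limit 36.9%.
- One affected and kept, one event-free participant removed: 1/9 = 11.1% (0.28% to 48.25%).

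**Step 4. How often could the question arise?** The chance of at least one affected participant among 10 is 1 − (1 − p)^10. For assumed per-patient risks p of 5%, 10% and 20% this is 40%, 65% and 89%. These are chances that someone has an event, not that anyone is then removed.

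**The case against.** A reader might infer from Figure 2 that anyone with a severe event or a worrying visit 3 scan is struck from the analysis. The documents do not support that. Figure 2 is a flowchart of trial conduct, its caption never mentions the analysis, and its footnote speaks of discontinuation. The section that defines the analysis set keeps participants who stop, and Table 2 has a cessation column with clinical, laboratory, ECG and CT data. For participants who reached 3.0 g/d, this part of the objection stands: the caption is loosely worded and is not a competing rule.

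A reader might also infer that the caption always flatters tricaprin. It does not. Withdrawals are on the list, and dropping an event-free one raises the rate, as the 1/9 case shows.

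It can further be said that ineligible cases naturally means failures of Table 1 found at screening, since Table 2 confirms eligibility only there. The CT section also expects participants whose renal function has fallen to the Table 1 limit by visit 4 to go on to visit 5, so Table 1 is not applied mechanically during treatment. That is probably the intent. But the analysis-set section does not say so, the caption says any visit, and Table 1 contains a discretionary criterion.

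Finally, how such cases are adjudicated may be left to the full protocol or the analysis plan. The article, however, states the set and the removal itself, and the two texts together permit what *Study design* rules out.

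**Conclusion.** The point holds in limited form. As written, a dosed participant declared ineligible after dosing can leave the only set described for the primary safety endpoint, and their adverse events leave with them. This contradicts the stated evaluation of all adverse events throughout the trial. For severe events, visit 3 CT findings and withdrawal after 3.0 g/d is reached, there is an ambiguity in the caption and no stated loss.

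The size rests on assumed event counts and on the affected person being the one removed. Under those assumptions one reclassification changes the primary result from 10% to none observed, and the exact upper limit from 44.5% to 33.6%. Nothing in the documents says that such a reclassification is planned. No test or decision threshold is affected, because none is specified.

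The loss of participants who never reach 3.0 g/d is a separate matter that the article states explicitly; this point does not depend on it.

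**What to change.** 1. *Determination of the target for data analysis*, primary safety endpoint: state that no dosed participant is removed for ineligibility, and that ineligible cases are listed with their adverse events.
2. Same section, secondary endpoints: limit ineligible cases to a Table 1 criterion that was already violated before the first dose and is judged on pre-dose data only.
3. Figure 2 caption: use *excluded* for pre-dose screen failures only. For each post-dose reason, write that the participant is discontinued and that events are still counted.
4. Reconcile the caption with *Treatment protocol and study assessments*, *Criteria for cessation of the protocol treatment* and the analysis-set section, so that each post-dose reason has one stated consequence for the analysis.

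The cost is a few sentences. No new data are needed and no clinical stopping rule has to change. The wording should be settled before the data are analysed, so that the choice of who is counted does not follow the results.
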